### Interventions

2.3

Patients will be randomized for 2 types of femoral cemented stem prostheses: the Exeter V40 cemented femoral stem [Stryker Orthopedics, Mahwah, NJ] for the thick-layer cement technique, and Müller straight stem [Zimmer, Winterthur, Switzerland] for the “French paradox” technique. These cemented stem prostheses used for THA are the ones used in our clinical practice.

As aforementioned, the study's main goal is to assess postoperative bone metabolism and bone morphology in patients who underwent THA. Therefore, SPECT-CTs will be performed. ^99^Tc-MDP SPECT-CTs will be performed as an additional complementary imaging test at 3, 6, 12, and 24 months after the surgical procedure. The acquisition field will be from the pelvis to the distal third of the femur, including the distal end of the prosthesis.

The SPECT-CTs study will combine bone metabolic activity and morphological assessment through the acquisition of SPECT-CT hybrid tomographic scans. The SPECT-CT will be performed with the *Discovery NM/CT 670* scan (*GE Healthcare, Waukesha, WI*). It has a dual-detector, free-geometry integrated nuclear imaging camera and a 16-head CT configuration.

Images’ acquisition will be performed as follows:

Early phase: Planar dynamic images acquisition in vascular phase, injecting under the camera, in anterior and posterior projections.^[8]^ Acquisition parameters are Matrix 64x64, 2 seconds fm/60’.Immediately afterwards, a SPECT acquisition will be performed at an early stage in continuous “Step and shoot” mode, 7” fm/60 images per head (3° of rotation). Total acquisition: 7 minutes, Matrix 128x128, Zoom x1. No CT acquisition will be made.Late phase: Planar static images acquisition in anterior and posterior projection, 256x256 matrix, Zoom x1, for a period of 10 minutes. SPECT/TC: “Step and shoot” mode, 2” fm/60 images per head (3° of rotation). CT 120 kV, modulated mA (80-180) cuts 1.25 mm, matrix 512x512.

Image reconstruction uses Matrix 512x512, OSEM (*Volumetrix MI Evolution* for Bone, *GE Healthcare*) 128x128 and 4.4 mm pixel on each axis. OSEM iterative reconstruction (number of iterations 4, maximum of OSEM subsets 10). Periprosthetic activity quantification will be performed by applying regions of interest (ROIs) dividing the areas into segments, in both the acetabular and femoral components.^[9]^

Since the cement layer progressively attaches to the bone, a longitudinal evaluation must be performed. Risk of prosthetic loosening will be assessed according to the Harris Radiographic Loosening Risk Classification (Table S5, Supplemental Digital Content).[^10^,^11^]

Plain Radiographies will be assessed separately by 2 different physicians within the study team. In case of any discrepancies between their assessments, both physicians will discuss the plain radiographies until reaching a consensus. This consensus will be adopted as the final assessment.

Clinical outcomes of THA will be assessed by comparing patients’ pre- and postoperative answers to Harris Clinical Assessment scale (see Table S1, Supplemental Digital Content),[^12^,^13^] to Merle d’Aubigné Clinical Assessment Scale (see Table S2, Supplemental Digital Content),[^12^,^14^] and to Western Ontario and McMaster Universities Arthritis (WOMAC's Index) (Western Ontario and McMaster Universities Arthritis) (see Table S3, Supplemental Digital Content).^[15]^ Results in terms of quality of life will be assessed by comparing patients’ pre- and postoperative answers to the EuroQoL-5D-3L© questionnaire (see Table S4, Supplemental Digital Content).^[16]^

### Criteria for discontinuing or modifying allocated interventions

2.4

Given the characteristics of this clinical trial, once the prostheses have been placed, the assigned interventions cannot be modified.

On the other hand, since the SPECT-CT scans will be performed to all enrolled patients, no modifications are anticipated. Participants may voluntarily discontinue their participation in the clinical trial for any reason, at any time. The investigator may also decide at any time during the trial, to temporarily interrupt or permanently discontinue the patients’ participation in the clinical trial if it is deemed that continuation would be detrimental to, or not in the best interest of the participant.

Similarly, the ethics committee or authorized regulatory authority can decide to halt or prematurely terminate the trial when new information becomes available whereby the rights, safety and well-being of trial participants can no longer be assured, when the integrity of the trial has been compromised, or when the scientific value of the trial has become obsolete and/or unjustifiable.

### Strategies to improve adherence to intervention

2.5

As above mentioned, once the prostheses have been placed, the assigned interventions cannot be modified.

A team member will be responsible for programming and calling the patients in order to perform all planned control visits according to the protocol, scheduling the SPECT-CT and the planned questionnaires: Harris Hip Score, Merle d’Aubigné Score, WOMAC Index and EuroQoL-5D-3L©. Besides, a text message/phone call/email will be sent to the patients reminding them of the control visits 24 hour in advance.

### Relevant concomitant care permitted or prohibited during the trial

2.6

Since in our hospital only 2 types of femoral cemented stem prostheses are available (Exeter V40 cemented femoral stem and Müller straight stem), which will be used in this clinical trial, it is not expected to use other femoral cemented stem prosthesis. The postoperative care (inpatient and outpatient) will be performed according to our clinical practice.

### Outcomes

2.7

Study primary and secondary outcomes are summarized in Table 2.

**Table 2 T2:** Summarized primary and secondary study outcomes.

Primary outcomes
Bone metabolic activity: number of counts per image set (median and its 95% CI) in the SPECT study. *Note: Counts per image set are a measure unit defined as the number of photons captured by the gamma camera, which represent the radiopharmaceutical uptake.* *SPECT will be performed at 3, 6, 12, and 24 mo of the intervention.*
Bone morphology: Alignment angles (median and its 95% CI) in the plain radiography and in the CT scan study. *Note: Alignment angles will be measured in degrees using the anatomical axis of the femur as a reference. Stem deviations from the femoral anatomical axis will be classified as “Varus” (if the tip of the stem is situated laterally to the femoral anatomical axis) or as “Valgus” (if the tip of the stem is situated medially to the femoral anatomical axis).* *Plain radiography will be performed at baseline and at 3, 6, 12, and 24 mo of the intervention.* *CT Scan will be performed at 3, 6, 12, and 24 mo of the intervention.*
Secondary outcomes
Axial displacement (median and its 95% CI) in the plain radiography and in the CT scan study. *Note: Axial displacement will be measured (in millimeters) using the inter-teardrop line as a reference. In the CT Scan study, this inter-teardrop line will be measured on the coronal plane.* *Axial displacement will be assessed at 3, 6, 12, and 24 mo of the intervention.*
Prosthesis loosening risk: number (and proportion) of patients classified as “possibly loose”, “probably loose”, and “definitely loose”, according to the Harris Radiographic Classification of Loosening Risk. *Note: Possibly Loose: Presence of a radiolucent line of 50% to 99% of the cement-bone boundary; Probably Loose: Radiolucency line at 100% of cement-bone boundary; Definitely Loose: Stem migration or a fracture of the cement mantle.*
Clinical outcomes: Harris Hip Score (median and its 95% CI). *Note: Being a score of 100 points the best possible result, and a score of 0 the worst possible result.*
Clinical outcomes: Merle d’Aubigné Score (median and its 95% CI) *Note: Clinical grades (Very good, Good, Medium, Fair, Poor) are given by the scores of Pain and Walking ability and adjusted down 1 to 2 grades, depending on the mobility score.*
Clinical outcomes: WOMAC Index Score (median and its 95% CI) *Note: Being a score of 96 the best possible result, and a score of 0 the worst possible result.*
QoL: EuroQoL-5D-3L© questionnaire score (median and its 95% CI). *Note: Since results are coded from 1 to 3 for each dimension, “11111” is the best possible result and “33333” is the worst possible result.*

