### Trial design

1.4

This is a single center, randomized, controlled, pilot clinical trial in patients who undergo total hip arthroplasty surgery with implantation of a cemented prosthetic.

Those patients who accept to participate will have a plain radiography and a SPECT-CT, at 3, 6, 12, and 24 months of the intervention. These SPECT-CTs will be done in addition to the usual clinical practice complementary imaging exams and will require the administration of the ^99m^Technetium- methylene diphosphonate (^99m^Tc-MDP) radiopharmaceutical.

Since this is a study based on usual clinical practice, collection of existing information from medical records, and prospective evaluation of the SPECT-CTs, no significant risk is expected in advance for the patients enrolled. Besides, given the low doses of ^99m^Tc-MDP administered for this type of scan,^[6]^ radiation-induced adverse effects are extremely rare, especially in those over 60 years of age, which is the age-range of this study.^[7]^ However, an insurance cover will be hired, should any unforeseen problems arise because of the study.

The postoperative SPECT-CT follow-up results will be explained to each patient. After the 24-month SPECT-CT, the patients’ participation in the study will be terminated and usual clinical practice follow-up shall be provided as for the general population.

This study was registered in the ClinicalTrials.gov Protocol Registration and Results System (Identifier: NCT05010733, August 18, 2021).

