#### Study procedure

2.7.1

Participants will be screened among patients on the waiting list for THA. The screening will be carried out following the waiting list's order (i.e., the first patient on the waiting list will be contacted first, and so on, until the last patient on the waiting list is contacted or until the planned sample size has been reached, whichever comes first). Patients will be contacted by phone by a study team member, who will explain the study to them and answer any questions that may arise. If the patient accepts to participate, a screening visit will be scheduled.

On the day of “Visit 1”, the Study Information Sheet will be delivered to the patient and any other doubts that may arise will be answered. If the patient accepts to participate, he/she will be asked to sign the Informed Consent, a *sine qua non* condition for he/she to participate in the trial. Hereafter, all the information mentioned on Table 3 will be gathered and the complementary exams will be scheduled.

**Table 3 T3:** Participant timeline.

	Visit 1	Visit 2	Visit 3	Visit 4	Visit 5	Visit 6	Visit 7
	Patient screening	Day of surgery	Hospital discharge	3 (±1 wk) mo of the surgery	6 (±2 wks) mo of the surgery	12 (±1) mo of the surgery	24 (±1) mo of the surgery
Obtaining informed consent	✓						
Eligibility criteria assessment	✓						
Demographic data	✓						
General examination (1)	✓	✓	✓	✓			
General laboratory blood tests (2)	✓		✓	✓	✓	✓	✓
Randomization		✓					
SPECT-CT				✓	✓	✓	✓
Plain radiography	✓			✓	✓	✓	✓
Clinical outcomes: Harris Hip Score, Merle d’Aubigné Score and WOMAC index score	✓			✓	✓	✓	✓
QoL questionnaire	✓			✓	✓	✓	✓
Safety: adverse events	✓	✓	✓	✓	✓	✓	✓
Concomitant treatment recording				✓	✓	✓	✓

The institutional review board (IRB) approved the protocol on May 20, 2021 (code ICPS033/20). We estimate that we will need approximately 6 months to identify the study population, establish the surgical indication, include them on the waiting list and perform the surgery. The study will be carried out between 2021 and 2024.

By the moment of submitting this manuscript, participant recruitment (patients’ screening visit) was still in progress.

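### No image of the implanted stem is scheduled before month 3, so stem migration has no time-zero reference and the film called baseline is preoperative

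*Protocol article*

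**What the plan says.** All references are to the Protocol article.

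- **Section 2.7, Table 2, primary outcome of bone morphology.** The measure is the alignment angle of the stem against the anatomical axis of the femur: "Stem deviations from the femoral anatomical axis will be classified as" varus or valgus. The imaging times are "Plain radiography will be performed at baseline and at 3, 6, 12, and 24 mo of the intervention" and, for CT, "CT Scan will be performed at 3, 6, 12, and 24 mo of the intervention".
- **Section 2.7, Table 2, secondary outcomes.** "Axial displacement will be assessed at 3, 6, 12, and 24 mo of the intervention", in millimetres, using the inter-teardrop line. The top category of the Harris loosening classification is "Definitely Loose: Stem migration or a fracture of the cement mantle". No reference image is named for migration.
- **Section 2.7.1, Table 3.** The row "Plain radiography" is ticked at Visit 1 (screening) and at Visits 4 to 7 (3, 6, 12 and 24 months). It is blank at Visit 2 (day of surgery) and Visit 3 (discharge). On who attends Visit 1: "Participants will be screened among patients on the waiting list for THA".
- **Section 1.4, Trial design.** Participants "will have a plain radiography and a SPECT-CT, at 3, 6, 12, and 24 months of the intervention". No baseline or discharge film is mentioned there.
- **Section 2.14, statistical methods.** Alignment and axial displacement are summarised as a median with 95% CI for each stem type. The clinical and quality-of-life scores are summarised before and after the intervention; alignment and displacement are not described that way.

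**The concern.** The alignment angle, the axial position and stem migration are all properties of an implanted stem. A film taken while the patient is on the waiting list shows none of them, so a baseline film listed under stem alignment cannot serve as a baseline for that outcome.

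Migration is also a change of position, and a change needs a starting value. If the first usable image is at 3 months, any settling or tilting before then is absorbed into the first reading. The trial compares two cementation techniques, and section 2.3 says that evaluation must be longitudinal because the cement attaches to the bone progressively. What the stem does in the first months is therefore of interest. A stem that moved before month 3 and was stable afterwards could not be recognised as migrated from the scheduled films.

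**Working it through.** The document gives no figure to reproduce here. The check sets the schedules side by side.

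| Time | Stem in place? | Plain film (Table 3) | CT (Tables 2 and 3) |
|---|---|---|---|
| Visit 1, screening | No | Yes | No |
| Visit 2, surgery | Implanted that day | No | No |
| Visit 3, discharge | Yes | No | No |
| Visit 4, 3 months ±1 week | Yes | Yes | Yes |
| Visit 5, 6 months | Yes | Yes | Yes |
| Visit 6, 12 months | Yes | Yes | Yes |
| Visit 7, 24 months | Yes | Yes | Yes |

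1. **Usable films.** Of the 5 scheduled plain films per patient, 4 show a stem. None of those 4 falls before month 3.
2. **Length of the gap.** Three months is about 13 weeks, so with the ±1 week window the first view comes about 12 to 14 weeks after surgery. As a share of follow-up, 3/24 = 12.5%.
3. **What can be estimated.** For one patient, let A0 be the angle (or axial position) at the end of surgery, d the movement from then to month 3, and At the value at month t. Then A3 = A0 + d.
   - Observed: A3, A6, A12 and A24, and hence changes such as A24 − A3.
   - Not observed: A0, and hence d = A3 − A0 and total movement A24 − A0 = d + (A24 − A3).
4. **What an arm comparison at month 3 means.** A difference in A3 between arms may come from A0, from d, or from both in the same or opposite directions. Randomisation does not make A0 equal between arms, because placement happens after allocation and is part of the technique being compared.
5. **Loosening classification.** Section 2.14 reads the Harris classes on plain radiography. Radiolucent lines and a cement-mantle fracture can be looked for on a single film, so those elements do not need a starting position. The migration element does, and on the written schedule the earliest possible reference is the 3-month film.

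**The case against.** The strongest reply is that no planned analysis fails. Section 2.14 takes the median angle per arm, not change from baseline. Table 2 says that a film is taken at baseline, not that a stem angle is read from it. This stands: the primary morphology comparison from month 3 onward survives, as do changes after month 3, and the SPECT outcome is untouched.

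A reader might go further than the schedule allows and infer three things:

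- **That an arm difference arising before month 3 would be reported as zero, or that displacement would be understated by whatever fraction occurs early.** This would follow only if every measurement were reset to zero at month 3, and no section says so. The angle is read against the femoral axis and the axial position against the inter-teardrop line, both available on each film with a stem. Early movement is carried into the 3-month value, mixed with placement but not erased. The document also gives no figure for the share of movement that occurs early.
- **That the 16 screening films are lost outcome data.** No section promises a stem angle from them, and they can serve as a preoperative record.
- **That no early postoperative film exists.** Section 2.6 leaves postoperative care to local practice, section 2.11 draws data from the medical records, and section 2.2.2 excludes misalignment of the component, which suggests that someone looks at position after surgery. A routine film may well exist, but the document does not say so or name one as a reference.

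It can also be said that an article condenses a fuller protocol, and that the supplementary Harris table is not shown. That could excuse silence about a reading rule. It does not cover Table 3, which sets out visit by visit when films are taken and leaves surgery and discharge blank.

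**Conclusion.** The point holds in a limited form. As scheduled, no image shows the implanted stem until 3 months ±1 week, and the film labelled baseline predates the stem. Per-arm alignment and axial position at 3, 6, 12 and 24 months remain comparable, but they combine initial placement with early movement. Movement in the first 12.5% of follow-up cannot be isolated, and the migration route to definite loosening has no time-zero position.

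This touches one primary outcome in its labelling and interpretation, and two secondary outcomes (axial displacement and loosening class) in their reference point, for all 16 patients. How much early movement occurs cannot be sized from the document. The conclusion rests on the scheduled imaging alone; a routine postoperative film in the records would close most of the gap. For a small, mainly descriptive pilot this is a correction that should be made, not a flaw that invalidates the trial.

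**What to change.** 1. In Tables 2 and 3, label the Visit 1 film as preoperative and stop calling it the baseline for stem alignment.
2. Where the medical record already holds a routine film taken after surgery and before or at discharge, record its date and readings in the eCRF. Define it in Table 2 as time zero for alignment change, axial displacement and Harris stem migration.
3. Where no such film exists, take the 3-month image as the reference, describe these outcomes as change from 3 to 24 months, and state that earlier migration was not assessed.
4. Report for how many patients in each arm each reference was used, and do not pool changes measured from different starting points.
5. When reporting per-arm medians at month 3, say that they reflect placement and early movement together.

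The cost is a small amendment to two tables and one additional eCRF item. Step 2 asks for no new imaging, since it uses only films already in the record. Step 3 needs wording alone and narrows what the trial can claim.

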#### Study procedure

2.7.1

Participants will be screened among patients on the waiting list for THA. The screening will be carried out following the waiting list's order (i.e., the first patient on the waiting list will be contacted first, and so on, until the last patient on the waiting list is contacted or until the planned sample size has been reached, whichever comes first). Patients will be contacted by phone by a study team member, who will explain the study to them and answer any questions that may arise. If the patient accepts to participate, a screening visit will be scheduled.

On the day of “Visit 1”, the Study Information Sheet will be delivered to the patient and any other doubts that may arise will be answered. If the patient accepts to participate, he/she will be asked to sign the Informed Consent, a *sine qua non* condition for he/she to participate in the trial. Hereafter, all the information mentioned on Table 3 will be gathered and the complementary exams will be scheduled.

**Table 3 T3:** Participant timeline.

	Visit 1	Visit 2	Visit 3	Visit 4	Visit 5	Visit 6	Visit 7
	Patient screening	Day of surgery	Hospital discharge	3 (±1 wk) mo of the surgery	6 (±2 wks) mo of the surgery	12 (±1) mo of the surgery	24 (±1) mo of the surgery
Obtaining informed consent	✓						
Eligibility criteria assessment	✓						
Demographic data	✓						
General examination (1)	✓	✓	✓	✓			
General laboratory blood tests (2)	✓		✓	✓	✓	✓	✓
Randomization		✓					
SPECT-CT				✓	✓	✓	✓
Plain radiography	✓			✓	✓	✓	✓
Clinical outcomes: Harris Hip Score, Merle d’Aubigné Score and WOMAC index score	✓			✓	✓	✓	✓
QoL questionnaire	✓			✓	✓	✓	✓
Safety: adverse events	✓	✓	✓	✓	✓	✓	✓
Concomitant treatment recording				✓	✓	✓	✓

The institutional review board (IRB) approved the protocol on May 20, 2021 (code ICPS033/20). We estimate that we will need approximately 6 months to identify the study population, establish the surgical indication, include them on the waiting list and perform the surgery. The study will be carried out between 2021 and 2024.

By the moment of submitting this manuscript, participant recruitment (patients’ screening visit) was still in progress.

### Sample size

2.8

This pilot clinical trial is an exploratory study by nature. To our knowledge, there are no studies comparing bone metabolism evolution in the postoperative period of these 2 types of femoral stem prostheses with SPECT-CT. We have not proceeded to a formal sample size calculation. A total of 16 patients will be randomized (8 by group) in this clinical trial. This sample size is feasible and achievable with the available budget.

### Recruitment

2.9

As abovementioned, patients will be screened among those on the waiting list for THA. First, when contacted by the principal investigator (or whoever he assigns), a detailed explanation of the study will be provided, and patients will be asked whether they want to participate and whether they intend to commit with all the scheduled visits. Likewise, on visit 1, the study will be explained in detail once again (emphasizing that the surgical indication will not differ from usual clinical practice and that the SPECT-CTs will be performed as an additional complementary imaging test at 3, 6, 12, and 24 months after the surgical procedure), and their commitment to assist to all scheduled visits will be asked once more. Posteriorly, the patient will be once again asked if he/she wants to participate in the trial, and, if positive, he/she will be requested to sign the written informed consent. During the study, a text message/phone call/email will be sent to the patients reminding them of the control visits 24 hours in advance. Besides, patients will be able to contact the principal investigator by phone at any time (the phone number will be provided in the Patient Information Sheet).

